## Abstract

**Background:**

Chinese external therapy (CET) is a topical application with mainly Chinese herb medicine therapy with thousands of years of historical implications and is a clinical routine that is commonly used for relieving joint-related symptoms in patients with arthritis in Chinese hospitals. However, there is a paucity of modern medical evidence to support its effectiveness and safety. Thus, we propose to implement a randomized, double-blinded, placebo-controlled clinical trial in patients with rheumatoid arthritis (RA) using, as the experimental intervention, topical application of a hospital-compounded gel preparation of Tripterygium wilfordii Hook F (TwHF).

**Methods:**

This study will be an 8-week double-blinded, randomized, placebo-controlled clinical trial conducted at Guang’anmen Hospital in Beijing, China, and 168 patients with moderately active RA will be randomly assigned with a 1:1 ratio to apply a topical gel preparation containing TwHF or placebo. The primary outcome variable will be the proportion of subjects, by study group, to achieve a 20% improvement in the American College of Rheumatology criteria (ACR20) by week 8. Secondary outcome measures to be assessed at weeks 4 or 8 will include: measurement of ACR20 response rate at week 4, ACR50 response rate, the changes in DAS28 score, and joint synovitis classification assessment monitored by musculoskeletal ultrasound. Safety evaluations conducted at weeks 4, 8 and 12 will be based on spontaneous complaints by the study subjects, but special emphasis will be focused on cutaneous allergy and alterations of menstruation in premenopausal female participants. Statistical analyses will be performed using the intention to treat analysis data set.

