The safety evaluation will be accomplished by a face-to-face interview at the 4th and 8th weeks and by a a telephone-interview with the remote 12th week follow-up. Adverse experiences of interest will include: manifestations of cutaneous allergy (erythema, edema, itching) and gastrointestinal stimulation due to mucous membrane damage. In addition, because of the high frequency of reproductive system damage, the safety evaluation will focus on changes in menstruation patterns among premenopausal female participants. The relevant female participants will be asked a general question about whether they have observed any change in their menstruation pattern. Irrespective of how they answer that question, a series of follow-up questions will attempt to quantify any change in the menstrual cycle (extension, shortening or no change), or in the quantity of menstrual flow (increased, reduced, or unchanged). Blood and urine routine laboratory examinations, including glutamic-pyruvic transaminase, glutamic oxalacetic transaminase, creatinine and urea nitrogen will be accomplished at baseline and on the 8th week. Quantitative changes will be addressed on the record. Professional judgments regarding the severity of any given adverse effect and any recognized relationship between the adverse effect and the study interventions will be documented if any of the above safety measures are observed to fall beyond normal clinical or laboratory ranges.

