## Discussion

To date, only a small number of studies have documented the effectiveness of CET using any pharmacological agent. This clinical trial is designed as a double-blinded, randomized, controlled study of TwHF-based CET in a moderate active RA population with 8 weeks of observation. Considering the main clinical features of active RA to be joint swelling, tenderness, and pain, these are the clinical manifestations monitored using validated instruments. It is anticipated that topical compound TwHF gel will also be effective in controlling the clinical manifestations of RA and safe for use by RA patients.

In animal studies, TwHF microemulsion has been observed to imeliorate the severity of a murine adjuvant-induced arthritis model and to reduce the male reproductive toxicity and hepatotoxicity [14]. It is hoped that the topical use of TwHF as a clinical application of CET in RA patients will be found to be both safe and efficacious. Although TwHF and its extracts have shown good responses in patients with RA it is currently limited to use in elderly patients because of demonstrated reproductive toxicity. Safety observations from previous studies have shown that compound TwHF applied topically can cause cutaneous reactions which are reversible with discontinuation of the topical TwHF compound. In addition, increases in serum aminotransferase and alterations in menstruation among female patients have been reported [5, 6].

There are several aspects of the current study design that are different from previous CET clinical studies using this agent. Firstly, the design of dosage adjustment in this study will demonstrate whether the period of dosage reduction will bring additional benefits to the patients. In clinical practice, patients often continue to apply the effective medicine for an additional period in order to consolidate the efficacy, though there is no evidence to support this practice. Secondly, the follow-up assessment has rarely been included in CET research. Since oral preparations of THwF have often exhibited side effects, such as gastrointestinal and menstrual disorders, special emphasis has been placed upon an 4-week follow-up (to monitor at least one menstrual cycle).

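### The Abstract bases safety on spontaneous complaints, the Methods on interviews; how skin and gastrointestinal events are collected is stated inconsistently and should be fixed as solicited

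*Protocol article*

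**What the plan says.** Abstract, Methods paragraph: "Safety evaluations conducted at weeks 4, 8 and 12 will be based on spontaneous complaints by the study subjects". The sentence continues: "but special emphasis will be focused on cutaneous allergy and alterations of menstruation in premenopausal female participants".

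Outcome measurements, safety paragraph: "The safety evaluation will be accomplished by a face-to-face interview at the 4th and 8th weeks", with a telephone interview for the week 12 follow-up. Skin and gastrointestinal events are named in advance: "Adverse experiences of interest will include: manifestations of cutaneous allergy (erythema, edema, itching) and gastrointestinal stimulation due to mucous membrane damage".

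For menstruation the same paragraph sets out a procedure: "The relevant female participants will be asked a general question about whether they have observed any change in their menstruation pattern". It goes on: "Irrespective of how they answer that question, a series of follow-up questions will attempt to quantify any change in the menstrual cycle". Changes in menstrual flow are covered in the same way. Blood and urine tests, with liver and renal markers, are scheduled at baseline and week 8.

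The Discussion reports, from earlier studies, "cutaneous reactions which are reversible with discontinuation of the topical TwHF compound". It also mentions raised aminotransferase and menstrual changes. It gives no rates for any of these.

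**The concern.** The way adverse events are asked about largely determines how many are counted. Volunteered reports and answers to fixed questions give different totals, and an article that states both methods does not tell the reader which one will produce the safety table.

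The ambiguity falls mainly on skin and gastrointestinal symptoms. If those are recorded only when a patient raises them, mild events, and events that have cleared before the next contact, may go unrecorded in both groups. The absolute difference and the event counts would then be too small, which leans towards a conclusion of safety. The Background gives safety as one of the trial's aims, and the Discussion hopes to show a safe treatment.

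**Working it through.** **1. The two sections side by side.**

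| Type of event | Abstract | Outcome measurements |
|---|---|---|
| Menstruation | Spontaneous complaints, special emphasis | General question, then follow-up questions whatever the answer |
| Laboratory values | Not mentioned | Tests at baseline and week 8 |
| Skin (erythema, edema, itching) | Spontaneous complaints, special emphasis | Named as of interest within an interview; no question or recording rule given |
| Gastrointestinal | Spontaneous complaints | Named as of interest within an interview; no question or recording rule given |

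For menstruation, the Methods plainly replace the Abstract's description with solicited questions. For skin and gastrointestinal events they do not. The interview is a setting for collection, and what is asked in it about these events is not stated. The Abstract's emphasis on skin is an intention that the Methods turn into a procedure for menstruation only.

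**2. Could events fall between contacts?** The Intervention section has gel applied once a day from week 0, and the first safety contact is at week 4, so about 4 × 7 = 28 applications come before anyone asks. The Discussion says skin reactions reverse when the gel is stopped. A patient who reacts early, pauses and recovers could therefore have nothing to show at week 4. The Quality control section records reasons for withdrawal, which would catch patients who leave because of a reaction but not those who pause and stay. This shows that a gap is possible. It does not show how often it would occur.

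**3. Direction of the effect.** Let the true rates be p1 (TwHF) and p0 (placebo), and let a share c of events be captured equally in both blinded groups.
- Observed risk difference = c × (p1 − p0), which shrinks in proportion to c.
- Observed risk ratio = (c × p1)/(c × p0) = p1/p0, which is unchanged.
- Expected events per group = 84 × c × p, so counts fall and precision with them.

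**4. Illustration only.** The plan has no figure to reproduce here. All rates and capture shares below are assumed. The 84 per group is from the Sample size section. Power is for a two-sided test of two proportions at 0.05, by approximation, and is rough where counts are small.

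| Assumed true rates | Capture | Expected events | Risk difference (points) | Power |
|---|---|---|---|---|
| 10% v 2% | 100% | 8.4 v 1.7 | 8 | 59% |
| | 75% | 6.3 v 1.3 | 6 | 47% |
| | 50% | 4.2 v 0.8 | 4 | 33% |
| 20% v 5% | 100% | 16.8 v 4.2 | 15 | 84% |
| | 75% | 12.6 v 3.2 | 11.25 | 71% |
| | 50% | 8.4 v 2.1 | 7.5 | 52% |
| 30% v 5% | 100% | 25.2 v 4.2 | 25 | 99% |
| | 75% | 18.9 v 3.2 | 18.75 | 96% |
| | 50% | 12.6 v 2.1 | 12.5 | 82% |

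Incomplete capture would matter if it occurred. The documents supply neither the rates nor the capture share.

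**The case against.** The strongest reply is that this is a loose phrase in an abstract. The Methods describe scheduled interviews and list skin signs and gastrointestinal stimulation in advance, which does not read as collection by volunteered report alone. The Abstract itself qualifies the phrase by naming cutaneous allergy first among its emphases. The fuller menstrual wording has its own reason, reproductive toxicity, and menstrual change needs to be quantified. A condensed article may leave question wording to the Case Report Form and operating procedures that the Quality control section mentions.

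Much of this stands. That the interview does not ask about skin is an inference, and missing question wording alone would be no finding. What remains is that the article positively states a method, spontaneous complaints, which its own Methods do not follow for menstruation and do not clearly replace for skin and gastrointestinal events.

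Three stronger readings are tempting, and the documents do not support them:
- *Skin reactions are the main expected harm.* The safety paragraph puts its focus on menstruation, and the Discussion lists skin, liver enzyme and menstrual effects without rates or ranking.
- *Under-counting is certain.* Nothing in the text says that patients fail to report reactions. Staff also see patients at weeks 4 and 8, and reasons for withdrawal are recorded.
- *Skin and menstrual harms must be collected comparably.* No comparison between the two is planned. The comparison that matters is between blinded groups under the same procedure.

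**Conclusion.** The point holds as an inconsistency with a possible consequence. The Abstract and the Outcome measurements section describe different ways of collecting adverse events. For skin and gastrointestinal symptoms the only explicit method is the weaker one. If that method is used, mild or resolved reactions may be missed in both groups. With equal capture the risk difference shrinks in proportion to the share captured, while the risk ratio does not change. The size is unknown, because the article gives no reaction or capture rates; the table of assumed values shows direction only. The point deserves correction before data collection because safety is a stated aim and the remedy is cheap. If the Case Report Form already contains fixed skin and gastrointestinal questions, only the article's text needs correcting.

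**What to change.** Make the Abstract and the Outcome measurements section state one method, solicited collection, for all the adverse experiences of interest:
- At weeks 4, 8 and 12, ask every participant in both groups the same fixed questions on skin (erythema, edema, itching) and gastrointestinal symptoms.
- Cover the whole interval since the last contact, not only the day of the interview.
- Ask whether gel use was paused during that interval, and why.
- Keep spontaneous complaints as an addition, and report solicited and spontaneous events separately.

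The cost is a short checklist at contacts already planned, with no extra visits. Reported event rates will be higher in both groups, and the report should say that this follows from asking. Inspecting treated skin during the joint examination is not needed for this fix. Because one staff researcher makes all the outcome assessments, it could also affect that assessor's blinding.

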**Discussion:**

This proposed clinical trail is designed to evaluate the efficacy and safety of CET based on a single topically-applied agent in a relatively large patient population with RA. This study protocol gives a detailed description of the usage and dosage of the topical compound TwHF gel and the methodology of this study. In addition, it is hoped that the outcomes of this study will be viewed as supporting the generalizability of CET in the setting of inflammatory rheumatic diseases. The results of this study are expected to have important public health implications for Asian RA patients that currently utilize CET as a complimentary treatment.

**Trial registration:**

Clinical trial gov Identifier: NCT02818361. Registrated on Jun. 15, 2016.

## Background

Rheumatoid arthritis (RA) is a chronic, systemic disorder characterized by persistent synovitis involving diarthrodial joints. Uncontrolled active RA can result in joint damage, disability, decreased quality of life, cardiovascular disease, and other comorbidities. Although Non-Steroid Anti-Inflammatory Drugs (NSAIDs) and steroids have been recommended by many physicians to relieve joint pain, and other symptoms related to the chronic synovitis and systemic inflammation, those drugs carry an increased potential for side effects [1] and are poorly tolerated by many patients.

For centuries in China, Chinese external therapy (CET) has been an accepted clinical approach for relieving joint-related symptoms and has been well-received by Chinese RA patients. In a narrow sense, CET is a pharmacological treatment for body surface or skin (mucosa) diseases, such as fumigation and plaster, etc.. CET has a long history that has its origins in the earliest experience of Chinese Medicine during the Chinese Qin and Han dynasties (BCE 221 to CE 220). It was observed that RA symptoms typically present as the swelling of multiple limb joints, pain, and stiffness, the main presenting clinical manifestations of active RA exist near the skin surface. CET is believed to have a rapid and favorable effect because it can be applied directly above the lesions. However, there are very few modern evidence-based data to support its effectiveness and safety in active rheumatic diseases.

Tripterygium wilfordii Hook F (TwHF), a traditional Chinese herb, has been used to relieve joint pain for a thousand years in China and its extracts have recently proven to be effective in patents with RA [2, 3]. However, the oral application of TwHF is limited for clinical use because of its high frequency of reproductive system damage [4]. In order to reduce toxicity without losing efficacy, the current study utilizes a topical rather than an oral compound THwF, hoping to thereby explore the advantages of CET. We previously conducted a 4-week double-blinded, randomized, placebo-controlled pilot clinical trial on topical compound TwHF with 70 RA patients whose joint disease was severely-active. The findings of the pilot study showed that joints pain and swelling were rapidly (within one week) reduced with the application of topical compound TwHF twice a day. Furthermore, a favorable control of the overall RA disease condition was found, as the rate of achievement rose to 20% and 50% improvement in the (ACR20 and ACR50) were 34% and 17% at week 4, using intention to treat analysis [currently awaiting publication]. The ACR20 and ACR50 response rates were found to be even higher in another study which reported responses of 58% and 20% with the TwHF group at week 6 [5]. Additionally, a previous double-blind, randomized multicenter trial found that based upon methotrexate or leflunomide, 75 out of 87 patients (90.8%) in the topical compound TwHF group and 58 out of 87 patients (69.0%) in the topical placebo-treated group reported relief from their joint pain [6].

Encouraged by the above results, we have developed the topical compound TwHF to be used as a hospital gel preparation. Thus, we plan to undertake an 8-week double-blinded randomized placebo-controlled clinical trial to further explore the safety and effectiveness of topical TwHF gel in patients with active RA.

It is important to examine whether topical treatment, with TwHF gel, as a supplement to usual care, will result in better outcomes for patients with active RA. We expect a favorable outcome for the topical compound TwHF gel that supports its efficiency. This article provides a full description of the study’s design and methodology in accordance with the SPIRIT guidelines for reporting protocols for intervention trials and the CONSORT guidelines [7, 8] for reporting outcomes.

## Methods

### Study design

This clinical trail will be accomplished at Guang’anmen hospital, China academy of Chinese Medical Science in Beijing, China. The current study follows the guidelines of the Declaration of Helsinki for humans and has been approved by the ethic s committee of Guang’anmen Hospital (approval number: 2016–062-KY). Enrolled will be 168 patients with documented moderately active RA who will be randomized (1:1 ratio) to one of two treatment groups: the TwHF gel group and the placebo gel group. Written signed consent will be obtained from each participant before any study-related procedures are initiated.

### Participants

#### Inclusion criteria

Eligible patients, men and women, must age from 18 to 65 years old, and must be clinically diagnosed with RA prior to screening for study entry in accordance with the 1987 revised criteria of the American College of Rheumatology [9]. Their RA disease stage must be in the moderate activity range, as defined by the criteria of the 28-joint count Disease Activity Score (DAS-28 score), ranging between 3.2 to 5.1 [10]. If patients are receiving a disease-modifying, anti-rheumatic drugs (DMARDs), those medications should be continued unchanged throughout this study, but their dosages must have been stable for at least 12 weeks prior to study entry.

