### Intervention

The ingredients for the compounding of the topical TwHF gel include: Tripterygium wilfordii Hook F, Mangxiao (Mirabilite), Chuanxiong (Rhizoma Ligustici), Ruling (Olibanum), and Moyao (M yrrh) (proportions: 4:4:2:2:1). The topical placebo gel is made of a viscous agent and sucrose which make it looks like the active preparation. Both of the gels will be prepared by the Pharmaceutical Department of Guang’anmen Hospital, and the herbs will be purchased from Beijing Fengtaijinyuan Pharmaceutical Co., Ltd. Each gel is 20 gram (g) per tube. Both the topical compound TwHF gel and the placebo gel will be applied for 1st to 5th metacarpophalangeal joints, 1st to 5th proximal interphalangeal joints, wrists, knees and ankles 10 g for 1 h, once a day from week 0 through week 4 and 10 g from week 5 through week 8.

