### Outcome measurements

Outcomes measurements will be assessed at baseline, at week 4, at week 8 and at the 12th week follow-up. The DAS28 joints will be assessed for swelling and tenderness by a trained staff member. All the outcome assessments will be accomplished by the same staff researcher.

The primary outcome measure will be ACR20 criteria [11] by week 8. To achieve ACR20, a patient must have a 20% or greater reduction in the number of both tender and swollen joints and a 20% or more improvement in 3 or more of the following: the physician’s or patient’s assessment of global health status, the patient’s assessment of pain on a visual analogue scale, the patient’s assessment of function using a modified version of the Health Assessment Questionnaire (HAQ), and the erythrocyte sedimentation rate (ESR) or serum C-reactive protein (CRP) level.

Secondary outcome measures will include: ACR20 assessed at week 4, ACR50 criteria assessed at weeks 4 and 8, changes at weeks 4 and 8 in DAS28, and joint synovitis classification. Since the DAS28 is a combined index to measure the disease activity in patients with RA, it can be used in combination with the European League Against Rheumatism response criteria [10]. In the present trial, the DAS28 score will be calculated, based on either the C-reactive protein (DAS28-CRP) or the erythrocyte sedimentation rate (DAS28-ESR) [10]. Changes in joint synovitis classification will be determined by serial musculoskeletal ultrasound (MUSU) focused on the total sum of synovitis classification based on the joint used gels. The MUSU synovitis classification will derive from each MUSU measurement as follows: 0 level, no doppler synovial tissue signal; level 1, three independent points or 2 successive or 1 to 2 independent dot doppler synovial tissue signals; level 2, doppler signal indicating <50% of the area representing synovium; level 3, doppler signal indicating synovium in >50% of the measured area [12].

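### Entry on DAS28 alone, with no minimum joint count, can admit patients who cannot meet ACR20; this dilutes the comparison but does not bias it

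*Protocol article*

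**What the plan says.** Under Inclusion criteria, the activity requirement is a DAS28 in the moderate band, "as defined by the criteria of the 28-joint count Disease Activity Score (DAS-28 score), ranging between 3.2 to 5.1". The other inclusion conditions are age, a stable DMARD dose where one is taken, and a diagnosis: patients "must be clinically diagnosed with RA prior to screening for study entry in accordance with the 1987 revised criteria" of the American College of Rheumatology. A diagnosis made before screening sets no joint count at entry. The Exclusion criteria set none either.

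Under Outcome measurements, the joint part of the primary endpoint is mandatory: "To achieve ACR20, a patient must have a 20% or greater reduction in the number of both tender and swollen joints". Improvement in three or more of the other listed measures is needed as well. The same section says that "the DAS28 is a combined index to measure the disease activity in patients with RA", allows it to be computed from either CRP or ESR, and states that "The DAS28 joints will be assessed for swelling and tenderness by a trained staff member". The Inclusion criteria do not say which version governs entry. The article gives no rule for a patient whose baseline tender or swollen count is zero.

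**The concern.** The entry score and the endpoint treat joint counts differently. DAS28 adds its components, so a high ESR or a poor global rating can make up for an absent joint count. ACR20 does not allow that: both counts must fall. A patient can therefore be in the DAS28 band with no swollen joint, or no tender joint, and be unable to respond whatever the gel does.

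Such patients take up sample size and add nothing to the primary comparison. They also pull down both reported response rates, which makes those rates harder to interpret. The planning rates make this more relevant. The 34.3% under Sample size agrees with the 34% reported in the Background for a pilot in severely active disease. This trial caps DAS28 at 5.1, where low or zero counts are more plausible, and the sample size makes no allowance for them.

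**Working it through.** **Inputs.** From the article: DAS28 band 3.2 to 5.1; ACR20 34.3% against 12.5%; 76 per group before dropout and 84 recruited; significance level 0.05; Pearson test; intention-to-treat analysis. Assumed: a two-sided test, the usual DAS28 weights, and the share f of patients with a zero count.

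**1. The plan's own figure.** With P = (0.343 + 0.125)/2 = 0.234 and a difference of 0.218, the usual two-sided formula at 80% power is

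n = 2(1.960 + 0.842)² P(1−P)/d² = 2 × 7.85 × 0.1792 / 0.0475 ≈ 59 per group.

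The formula as printed has a further factor of 2 and gives about 118.4, so 119. Neither equals 76. That is a separate matter, and the present point does not depend on it. It does mean that 76 per group has more than 80% power at the planning rates.

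**2. Can a patient with a zero count enter?**

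DAS28-ESR = 0.56√TJC + 0.28√SJC + 0.70 ln(ESR) + 0.014 GH

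DAS28-CRP = 0.56√TJC + 0.28√SJC + 0.36 ln(CRP + 1) + 0.014 GH + 0.96

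Here TJC and SJC are the tender and swollen counts and GH is the global rating.

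- 4 tender, 0 swollen, ESR 20, GH 40: 1.12 + 0 + 2.10 + 0.56 = 3.78. Eligible.
- 4 tender, 0 swollen, CRP 10, GH 40: 1.12 + 0 + 0.86 + 0.56 + 0.96 = 3.50. Eligible.
- 0 tender, 4 swollen, ESR 30, GH 50: 0 + 0.56 + 2.38 + 0.70 = 3.64. Eligible.
- 0 tender, 4 swollen, CRP 20, GH 50: 0 + 0.56 + 1.10 + 0.70 + 0.96 = 3.32. Eligible.
- 0 tender, 0 swollen, ESR 60, GH 50: 2.87 + 0.70 = 3.57. Eligible.
- 0 tender, 0 swollen, CRP 20, GH 50: 1.10 + 0.70 + 0.96 = 2.76. Not eligible.

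One zero count is compatible with entry on either version. Two zero counts depend more heavily on the version and on the other components.

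**3. Effect on the endpoint.** A baseline of 0 cannot be reduced by 20%, so ACR20 is not met in either arm. If a share f of each arm is in this position and the planning rates hold in the rest, both rates and their difference are multiplied by (1 − f). At f = 10%: 0.343 × 0.9 = 30.9% and 0.125 × 0.9 = 11.3%. At f = 20%: 27.4% and 10.0%.

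**4. Power.** Exact power of the Pearson test, found by summing binomial probabilities over all tables with p < 0.05 (two-sided):

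| f | Rates | 76 per group | 84 per group |
|---|---|---|---|
| 0 | 34.3% / 12.5% | 90.3% | 93.0% |
| 10% | 30.9% / 11.3% | 86.1% | 89.5% |
| 20% | 27.4% / 10.0% | 80.9% | 84.6% |
| 30% | 24.0% / 8.8% | 74.3% | 78.0% |

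The pooled normal approximation is slightly lower: at 76 per group, 85.0% for f = 10% and 79.3% for f = 20%. The 84 column applies if all randomised patients are analysed, as intention to treat implies. The 76 column applies if dropouts contribute no information.

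**The case against.** The strongest reply is that a patient built on paper does not show that such patients are common. The documents contain no joint-count data, so f is unknown. With 84 per group and the planning rates, power stays above the planned 80% at f = 20% and is lost only somewhere between 20% and 30%. This stands, and it limits the weight of the point.

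A reader might infer that the trial is underpowered for this reason. The documents do not support that: it would need both a large f and a figure for it, and neither is given.

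A reader might also infer bias. That does not follow. Randomisation spreads these patients over both arms and they are non-responders in each. Type I error is unaffected, and the comparison remains fair for the population the protocol chose.

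The treated sites listed under Intervention ("1st to 5th metacarpophalangeal joints, 1st to 5th proximal interphalangeal joints, wrists, knees and ankles") may suggest a further group, whose active joints are counted but receive no gel. The article does not list the 28 joints, and these patients are not barred from meeting ACR20. The same is true of patients with very few joints: one joint may decide their response, but they can respond. Neither group belongs in f.

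Finally, an article condenses a full protocol, which might contain a joint minimum. But the eligibility criteria are set out here in full sentences, and the point concerns a criterion as stated.

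**Conclusion.** The point holds in limited form. Followed as written, the entry criteria can admit patients who cannot meet the primary endpoint, and the article has no rule for them. The consequence is dilution of both response rates and of the difference.

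The size depends on f, which is undocumented. At the planning rates, with 84 per group, power falls from 93.0% to 89.5% if f is 10% and to 84.6% if f is 20%. These figures rest on the usual DAS28 weights, a two-sided 0.05 level, and the pilot rates holding among patients who can respond. The last is the weakest assumption, since the pilot enrolled severely active disease. If true rates differ less than planned, there is less spare power to absorb the dilution.

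Severity is minor to moderate. It is worth correcting because the correction is cheap, not because the trial fails without it.

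**What to change.** Add to the Inclusion criteria: at least one tender and at least one swollen joint at baseline, among the joints counted for ACR20. One of each is all that is needed to remove the certain non-responders. The sponsor may set a higher minimum, or restrict it to joints that also receive gel, but nothing in the documents requires either.

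The joint counts are already needed to compute DAS28, so no new assessment is involved. The cost is an eligibility amendment, a small number of additional screen failures (the number cannot be estimated from the documents) and a slightly narrower population. If patients have already been enrolled, or the criteria cannot be changed, the protocol should at least state how a zero baseline count is handled when ACR20 is derived, and the number of such patients should be reported by arm.
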